# Induction chemotherapy followed by chemoradiotherapy *versus* chemoradiotherapy alone as neoadjuvant treatment for locally recurrent rectal cancer: study protocol of a multicentre, open-label, parallel-arms, randomized controlled study (PelvEx II)

**DOI:** 10.1093/bjsopen/zrab029

**Published:** 2021-06-05

## Abstract

**Background:**

A resection with clear margins (R0 resection) is the most important prognostic factor in patients with locally recurrent rectal cancer (LRRC). However, this is achieved in only 60 per cent of patients. The aim of this study is to investigate whether the addition of induction chemotherapy to neoadjuvant chemo(re)irradiation improves the R0 resection rate in LRRC.

**Methods:**

This multicentre, international, open-label, phase III, parallel-arms study will enrol 364 patients with resectable LRRC after previous partial or total mesorectal resection without synchronous distant metastases or recent chemo- and/or radiotherapy treatment. Patients will be randomized to receive either induction chemotherapy (three 3-week cycles of CAPOX (capecitabine, oxaliplatin), four 2-week cycles of FOLFOX (5-fluorouracil, leucovorin, oxaliplatin) or FOLFORI (5-fluorouracil, leucovorin, irinotecan)) followed by neoadjuvant chemoradiotherapy and surgery (experimental arm) or neoadjuvant chemoradiotherapy and surgery alone (control arm). Tumours will be restaged using MRI and, in the experimental arm, a further cycle of CAPOX or two cycles of FOLFOX/FOLFIRI will be administered before chemoradiotherapy in case of stable or responsive disease. The radiotherapy dose will be 25 × 2.0 Gy or 28 × 1.8 Gy in radiotherapy-naive patients, and 15 × 2.0 Gy in previously irradiated patients. The concomitant chemotherapy agent will be capecitabine administered twice daily at a dose of 825 mg/m^2^ on radiotherapy days. The primary endpoint of the study is the R0 resection rate. Secondary endpoints are long-term oncological outcomes, radiological and pathological response, toxicity, postoperative complications, costs, and quality of life.

**Discussion:**

This trial protocol describes the PelvEx II study. PelvEx II, designed as a multicentre, open-label, phase III, parallel-arms study, is the first randomized study to compare induction chemotherapy followed by neoadjuvant chemo(re)irradiation and surgery with neoadjuvant chemo(re)irradiation and surgery alone in patients with locally recurrent rectal cancer, with the aim of improving the number of R0 resections.

## Introduction

Locally recurrent rectal cancer (LRRC) occurs in 6–10 per cent of patients who undergo intentionally curative surgery for primary rectal cancer^1^^,^^2^. To cure patients with LRRC, achieving a resection with clear resection margins (R0 resection) is imperative^2–8^. When an R0 resection is achieved, 5-year overall survival rates vary between 48 and 58 per cent, whereas a resection without clear resection margins (R1/2 resection) results in a 5-year survival rate of only 10–18 per cent. Moreover, incomplete resections are associated with 5-year local re-recurrence rates of 70–80 per cent, and often result in severe morbidity, poor quality of life, and/or death^5^^,^^6^^,^^9–13^. Unfortunately, the attempt to achieve an R0 resection often fails because of challenging anatomy due to previous surgery, the presence of fibrosis as a result of previous radiotherapy, and the involvement of other structures such as adjacent organs, pelvic sidewall, and sacrum. To increase the chance of achieving an R0 resection, neoadjuvant treatment with chemoradiotherapy is considered the standard of care in many institutions^14^. In patients who received pelvic radiotherapy previously, reirradiation with a dose of 30 Gy has been proven to be safe and effective^3^^,^^15^. Despite the use of neoadjuvant chemo(re)irradiation, R0 resections are achieved in only 60 per cent of patients^16^^,^^17^. Therefore, there is ongoing research to optimize the treatment strategy for patients with LRRC.

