### Interventions

Eligible patients who have signed informed consent will be randomized by the coordinating investigator in a 1 : 1 ratio using a software randomization program (ALEA Clinical; FormsVision, Abcoude, the Netherlands). Patients will be stratified for previous chemotherapy, previous radiotherapy, and expert centre. After randomization, the treating surgical oncologist will refer the patient to the medical oncologist (experimental arm) or radiation oncologist (control arm).

The study flow chart is shown in *Fig. 1*, and study interventions and timelines for patients allocated to the experimental and control arms in *Tables 1* and *2* respectively.

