#### Surgery

Surgery will be performed by experienced surgical oncologists within 10–14 weeks after completion of chemoradiotherapy. The type of surgery will depend on the location of the recurrence and involvement of adjacent structures, and will be left to the discretion of the surgeon. When deemed necessary and feasible by the surgeon and radiation oncologist, intraoperative radiotherapy may be administered by either intraoperative electron beam radiotherapy or high-dose-rate intraoperative brachytherapy^38^^,^^39^.

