### Sample size

Currently, an R0 resection is achieved in approximately 60 per cent of patients undergoing surgery after treatment with neoadjuvant chemoradiotherapy^16^^,^^17^. However, 25 per cent of patients who start neoadjuvant chemotherapy are not eligible for surgery owing to progressive disease: local progression, distant progression, or death from progression^12^. This means that an R0 resection is obtained in only 45 per cent of patients (75 per cent of 60 per cent) who start with intentionally curative treatment. The study hypothesis is that there will be a 15 per cent increase in the R0 resection rate (from 45 to 60 per cent) for patients in the experimental arm. A χ^2^ test with a 5 per cent two-sided significance level indicated that the study would have 80 per cent power to detect a significant difference of 15 per cent between the two groups (given that the percentage in the control group is 45 per cent) when the sample size in each group is 173 patients. With an expected dropout of 5 per cent, the total requirement was calculated as 364 patients.

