### Statistical methods

Demographics, patient, and tumour characteristics will be presented for each treatment arm. Continuous data will be reported as mean (standard deviation) or median (interquartile range or 95 per cent confidence interval), depending on the distribution. Categorical data will be reported as count with percentage. All statistical tests will be two-sided and *P* < 0.050 will be classified as statistically significant. Patients initially randomized but considered ineligible afterwards, based on information that should have been available before randomization, will be excluded from all analyses.

Analysis of the primary endpoint of this study, the proportion of patients with an R0 resection, will be based on the intention-to-treat principle using Fisher’s exact test. In addition, a per-protocol analysis will be performed as a sensitivity analysis.

All survival curves will be constructed according to the Kaplan–Meier method, and the log rank test will be used to compare treatment arms, adjusting for stratification factors at randomisation (previous radiotherapy, previous systemic therapy, and expert centre). In addition, hazard ratios will be calculated using a Cox proportional hazards regression model, adjusting for stratification factors. Metastasis-free survival, progression-free survival, and overall survival will be based on the intention-to-treat group. Local re-recurrence free survival and disease-free survival analyses will include only patients who underwent surgery.

Data on surgical characteristics, histopathological characteristics, and major surgical morbidity will be presented by treatment arm, and will be derived only for patients who underwent surgery. The number of patients undergoing surgery will be analysed in the intention-to-treat population. Comparison between treatment arms will be done by means of Fisher’s exact test.

The absolute and relative incidence of toxicities related to the administration of induction chemotherapy or chemoradiotherapy will be presented by treatment arm, and analysed in all patients who received at least one dose of neoadjuvant chemotherapy (experimental arm) or chemoradiotherapy (control arm). Comparison between treatment arms will be done by means of Fisher’s exact test.

Comparison of health-related quality of life between the two treatment arms at baseline and over time will be performed by means of a random-effects regression model and will be based on the intention-to-treat group.

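### Local tumour extent, which the protocol names as a reason R0 resection fails and which is assessable before allocation, is left out of the stated R0 and survival analyses, at a cost in precision but not validity

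*Protocol article*

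**What the plan says.** - **Prognosis.** The Introduction attributes failed R0 resection to anatomy after earlier surgery, fibrosis after earlier radiotherapy, and "the involvement of other structures such as adjacent organs, pelvic sidewall, and sacrum". The Surgery section expects trial operations to differ for the same reason: "The type of surgery will depend on the location of the recurrence and involvement of adjacent structures".
- **Availability.** Tables 1 and 2 mark pelvic MRI in the pre-allocation column for both arms. Under Recruitment, all eligible patients are reviewed by an expert-centre multidisciplinary team.
- **Randomisation.** Under Interventions: "Patients will be stratified for previous chemotherapy, previous radiotherapy, and expert centre". Of the reasons listed in the Introduction, only previous radiotherapy appears here.
- **Analysis.** Statistical methods names Fisher's exact test by intention to treat for R0, with a per-protocol sensitivity analysis. The log rank comparison is made "adjusting for stratification factors at randomisation (previous radiotherapy, previous systemic therapy, and expert centre"), and the Cox models adjust for the same stratification factors. The stated use of tumour characteristics is descriptive: "Demographics, patient, and tumour characteristics will be presented for each treatment arm".

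**The concern.** A baseline variable that the authors themselves regard as a cause of the primary outcome is available for every patient before allocation, but the named primary test does not use it. Nor does the stated adjustment set for survival. Adding the three stratification factors to the R0 analysis would still leave local extent out.

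The variation in R0 that extent could explain therefore stays in the error term. The confidence interval for the R0 difference is wider, and power lower, than the same 364 patients could give. If the arms happen to differ in sidewall or sacral disease, the baseline table would show it, but the stated analysis has no prespecified way to take it into account. An adjustment chosen after the data are seen, in an open-label trial, would carry less weight.

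**Working it through.** **1. The plan's own figure.** Inputs from Sample size: "5 per cent two-sided significance level"; "80 per cent power to detect a significant difference of 15 per cent between the two groups"; R0 "from 45 to 60 per cent". With mean rate 0.525 and pooled variance under the null:

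n = [1.960·√(2·0.525·0.475) + 0.842·√(0.45·0.55 + 0.60·0.40)]² / 0.15² = 172.8, so 173 per arm.

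Total: 346 × 1.05 = 363.3, so 364. Both stated figures reproduce.

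**2. Unadjusted precision.** Variance of the R0 difference, times n per arm: 0.45·0.55 + 0.60·0.40 = 0.4875. At 173 per arm SE = √(0.4875/173) = 0.0531, and power = Φ(0.15/0.0531 − 1.960) = 80.7%. This is the reference below; it uses the unpooled variance, hence slightly above 80.0%.

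**3. Precision with adjustment.** Assumptions, none of them in the documents: two extent groups; a share q of 40 to 60% in the worse group; a control R0 gap g between groups with the overall rate held at 45%; and a common odds ratio for treatment giving 60% overall in the experimental arm. For an R0 difference standardised over extent:

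V = Σ(group share) × [p_C(1−p_C) + p_E(1−p_E)] + ½·Var(treatment effect across groups)

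The last term is negligible here (at most about 0.0001).

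Example, q = 50%, g = 30 points: control 60% and 30%, experimental 74.5% and 45.5%.
V = 0.5·(0.240 + 0.190) + 0.5·(0.210 + 0.248) = 0.444. Ratio 0.444/0.4875 = 0.911, a cut of 8.9%. Power = Φ(0.15/√(0.444/173) − 1.960) = 84.2%.

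Over q = 40 to 60%:

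| Assumed R0 gap | Variance cut | Power at 173 per arm | Gain over 80.7% |
|---|---|---|---|
| 10 points | about 1% | 81.0% | about 0.4 points |
| 20 points | about 4% | 82.1–82.2% | about 1.5 points |
| 30 points | 8–9% | 83.9–84.2% | 3.2–3.5 points |
| 40 points | 14–16% | 86.3–87.0% | 5.6–6.3 points |

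Parametrising by odds ratio instead (0.5, 0.33 and 0.2; prevalence 30% or 50%) gives variance cuts of 2–3%, 6–7% and 12–14%, and power of about 82%, 83% and 85–86%.

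**4. How demanding the larger gaps are.** Sample size builds 45% as 75% reaching surgery × 60% R0 among those operated on. So 25 of the 55 points of R0 failure come from never reaching surgery. If extent does not affect who reaches surgery, then at q = 50% a 30-point gap requires R0 among operated patients of 60/75 = 80% against 30/75 = 40%. A 40-point gap requires 65/75 = 87% against 25/75 = 33%.

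**5. Chance imbalance.** At 182 per arm and q = 50%, the SD of the between-arm difference in prevalence is √(2·0.5·0.5/182) = 5.2 points. A difference above 5 points occurs in about a third of trials, and above 10 points in about 5 to 6%. With a 30-point gap, a 10-point imbalance moves the R0 difference by 0.10 × 30 = 3 points. The SE of that difference is √(0.4875/182) = 5.2 points, so the shift is just under 0.6 SE; for a 5-point imbalance it is 1.5 points, about 0.3 SE. This variation is already part of the SE in step 2 and is not an additional loss.

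**6. Validity of the planned test.** In 20,000 simulated null trials at 173 per arm with a strong ignored covariate (prevalence 50%, odds ratio 0.2), Fisher's test rejected in 3.6%. Its exact power for 45% against 60% is 76.0% at 173 per arm and 79.6% at 182, so it has no power in reserve. That shortfall comes from the choice of test and is a separate matter from extent.

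**The case against.** The strongest reply is that nothing here is an error. The Introduction is background, and naming a cause of failure does not oblige the trial to adjust for it. An unadjusted intention-to-treat test is valid and easy to read. The benefit rests on figures the documents do not give, and eligibility is limited to resectable disease, which may narrow the spread of extent. The one R0 rate by location in Current evidence, 85% in 13 patients with lateral recurrence after induction chemotherapy and chemoradiotherapy, is too small to settle anything but gives no support to a large deficit. MRI grading may also differ between international centres, and misclassification would shrink the gain.

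Much of this stands, and it rules out three stronger readings that a reader might infer:

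- *That the R0 comparison is biased or its type I error inflated.* It is not; step 6 shows the error rate is held.
- *That randomisation leaves extent unbalanced.* Randomisation balances it in expectation. Only stratification on it is absent, and chance imbalance is already counted in the standard error.
- *That no planned analysis uses extent.* The article condenses a fuller protocol, the statistical analysis plan is not shown, and the covariates of the quality-of-life model are not listed. The point covers only the primary test and the survival adjustment set that are stated.

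The objection does not remove the point itself. The article does not leave the primary analysis open: it names an unadjusted test for R0 while adjusting the survival analyses. Current evidence also explains disappointing R0 rates in earlier series by unfavourable baseline characteristics, so the authors themselves treat baseline prognosis as able to move this endpoint.

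**Conclusion.** The point holds as one of efficiency. The stated primary test and survival adjustment set omit a baseline factor that the protocol itself links to R0 failure and that can be assessed before allocation. Under assumed R0 gaps of 10 to 40 points, the cost is about 1 to 16% of the variance and under 1 to about 6 points of power at 173 per arm. The lower part of that range is modest, and the upper part needs a very strong prognostic effect.

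The figures assume two extent groups, a common odds ratio, accurate grading and large-sample variances. They compare adjustment for extent alone with no adjustment; the gain from extent beyond the stratification factors cannot be derived from the documents. The change is worth making because it is cheap and the planned test has no spare power, not because the present result would be invalid.

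**What to change.** - Record baseline MRI extent before randomisation as a simple coded variable, for example sidewall and/or sacral involvement yes/no, or three levels (no other structure; adjacent organ only; sidewall and/or sacrum).
- Prespecify the primary intention-to-treat R0 risk difference from a logistic model with previous radiotherapy, previous chemotherapy, expert centre (small centres pooled) and baseline extent, standardised to the trial population with a robust standard error.
- Report the unadjusted Fisher result alongside.
- Add extent to the Cox models for overall, progression-free and metastasis-free survival.
- Leave randomisation as it is; a further stratification factor on top of expert centre could make strata sparse.

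Cost: statistical wording and one coded field from imaging and a review already scheduled, with no extra patients, visits or scans. The downsides are that grading may vary between centres, which a short written definition would limit, and that a model-based estimate replaces a two-by-two table as the primary result.

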### Potential benefits and disadvantages of induction chemotherapy

Induction chemotherapy in addition to neoadjuvant chemo(re)irradiation has the potential to induce more local tumour downstaging than can be achieved with chemoradiotherapy alone owing to the supplementary effect of the induction chemotherapy, and possibly also the synergistic effect of induction chemotherapy and chemoradiotherapy^18^. Improved local downstaging may subsequently increase the R0 resection rate, which has been identified as the main prognostic factor for overall survival^6–8^. When local downstaging is excellent, a pathologic complete response (pCR) can be achieved, which is a predictive variable for survival in patients with LRRC^19^. With improved local downstaging, the proportion of patients with a pCR may also increase. Alongside the local effect, induction chemotherapy may also have the potential to eradicate micrometastases^20^.

The addition of induction chemotherapy also has potential drawbacks. First, induction chemotherapy is associated with toxicity^21^. Second, chemotherapy-induced morbidity could delay, reduce or prevent subsequent treatment with chemoradiotherapy and surgery. Third, when chemoradiotherapy is preceded by induction chemotherapy, the toxicity of chemoradiotherapy may be increased. Finally, the prolonged and intensified neoadjuvant course may influence the patient’s performance status and may have a negative effect on surgical morbidity and mortality rates. Furthermore, prolonged neoadjuvant treatment may increase the risk of disease progression and secondary unresectability.

### Current evidence

Induction chemotherapy, whether or not combined with neoadjuvant chemoradiotherapy, is increasingly being used in the treatment of LRRC, although evidence for this approach is lacking^22^. Several retrospective studies and phase II clinical trials^23–26^ performed to investigate the role of induction chemotherapy in patients with primary locally advanced rectal cancer (LARC) have reported high R0 resection rates. However, other studies^27–29^, including comparative studies, did not demonstrate superior R0 resection rates after the addition of induction chemotherapy to neoadjuvant treatment.

Several studies investigating this treatment regimen in LARC used pCR as the primary endpoint. As in the studies focusing on R0 resection rate, the results were mixed. Some studies described promising pCR rates, whereas others found no effect of adding induction chemotherapy with regard to the pCR rate^30–34^. Regardless of the effect of this treatment on the R0 resection or pCR rate, induction chemotherapy seemed feasible, with high rates of compliance with the chemotherapy as well as with the subsequent chemoradiotherapy, and acceptable toxicity and postoperative morbidity^28^^,^^33^^,^^35^.

The available literature regarding induction chemotherapy in addition to chemoradiotherapy for patients with LRRC is limited; currently only three retrospective studies^19^^,^^36^^,^^37^ have been published. The first study^36^, which focused on patients with lateral local recurrence, reported a high R0 resection rate of 85 per cent in a subgroup of 13 patients who were treated with induction chemotherapy followed by chemoradiotherapy. In the second and third studies^19^^,^^37^, 58 and 132 patients respectively underwent induction chemotherapy followed by chemo(re)irradiation. Both studies reported promising pCR rates of 17 per cent, but the R0 resection rates did not appear to have improved. However, in both studies induction chemotherapy was initially administered to patients with unresectable disease or prognostically unfavourable characteristics, which may have had a negative impact on the R0 resection rate.

### Rationale for the study

Although the real benefit provided by the addition of induction chemotherapy to chemoradiotherapy and surgery for LRRC has not yet been established, its use is nevertheless increasing^22^.

This study will randomize patients with LRRC to receive either induction chemotherapy followed by chemoradiotherapy and surgery (experimental arm) or chemoradiotherapy and surgery alone (control arm). As R0 resection is the single most important prognostic factor for survival in patients with LRRC, the main hypothesis to be tested will be an increase in the R0 resection rate in the experimental arm compared with the control arm.

## Methods

### Study design and setting

This is a multicentre, international, open-label, phase III, parallel-arms study that will randomize eligible patients in a 1 : 1 ratio to receive either induction chemotherapy followed by neoadjuvant chemoradiotherapy and surgery (experimental arm) or neoadjuvant chemoradiotherapy and surgery alone (control arm). The study is registered with ClinicalTrials.gov (NCT04389086), including the list of centres enrolling for the trial. Surgical treatments will be limited to centres that perform at least 10 resections of LRRC per year (expert centres). Induction chemotherapy and chemoradiotherapy will be administered in expert centres and selected non-expert centres. This is protocol version 4.0, dated 10 December 2020.

### Participants

Patients aged 18 years or older, with resectable histopathologically or clinically proven LRRC after previous partial or total mesorectal resection, with a WHO performance status of 1 or less will be eligible for study participation. Patients with distant metastases at the time of randomization or in the previous 6 months, those who have undergone chemotherapy and/or radiotherapy in the past 6 months, patients with any contraindication to chemotherapy and/or radiotherapy and/or surgery, and those with concurrent malignancies that interfere with the planned study treatment or the prognosis of resected LRRC, will be excluded.

